### Participants

#### Inclusion and Exclusion Criteria

Included will be children aged between 28 days and 18 years, where the treating clinician decides to treat for septic shock and administer intravenous antibiotics and an intravenous fluid bolus. Randomisation will occur after participants have received at least 20mL/kg fluid bolus in the last 4 h (or 1,000 mL fluid bolus in patients weighing over 50 kg), and the treating clinician must have decided to continue treating due to ongoing signs of shock. The exclusion criteria relate to patient characteristics which interfere with the study intervention and presence of chronic conditions which can interfere with the clinical outcome, as detailed in Table 1.

**Table 1 T1:** Inclusion and exclusion criteria.

**Rule**	**Criterium**	**Definition**
Inclusion	Age	• Aged ≥28 days and <18 years
	Illness	• Treated for sepsis
	Treatment	• Received at least 20 ml/kg fluid bolus in the last 4 h and clinician decides to continue treating signs of shock
	Consent	• Parental/caregiver consent prior to or after enrolment
Exclusion	Age	• Preterm babies born <34 weeks gestation that have a corrected age of <28 days
	Treatment	• Received ≥40 mL/kg of fluid boluses during the 4 h pre-enrolment • Inotrope infusion commenced pre-enrolment • Lack of access (intraosseous, central venous or peripheral) to administer fluids and/or inotropes after 60 min of enrolment
	Co-morbidities	• Cardiomyopathy or chronic cardiac failure • Chronic hypertension due to cardiovascular or renal disease, requiring regular antihypertensive treatment. • Known chronic renal failure (defined as requiring renal replacement therapy) • Known chronic hepatic failure • Palliative care patient/patient with limitation of treatment (not for inotropes, cardiopulmonary resuscitation, extracorporeal membrane oxygenation, intubation or ventilation)
	Illness severity	• Cardiopulmonary arrest in the past 2 h requiring cardiopulmonary resuscitation of >2 min duration, or death is deemed to be imminent or inevitable during this admission. • Major bleeding with haemorrhagic shock • Sepsis is not likely to be the cause of shock
	Previous study enrolment	• Enrolment in RESPOND study <6 months prior

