#### Standard Care

In the standard arm, patients will receive standard care as per site specific protocols based on international guidelines (11, 13). Specifically, patients in the standard arm will receive 40–60 mL/kg of fluid bolus therapy prior to initiating inotropes, thus, 20–40 mL/kg bolus fluid *after* randomisation (in addition to the 20 mL/kg bolus fluid, or 1,000 mL fluid bolus in patients >50 kg, which has to be administered to meet enrolment criteria). Further fluid and inotrope decisions in the standard care arm are at the discretion of the treating physician. The standard care is aligned with education provided at the study sites through the Paediatric Sepsis Pathway project (Queensland Sepsis collaborative) since 2018, which advocates for the administration of sepsis resuscitation bundles as per the Surviving Sepsis Campaign.

Patients who improve in <4 h can in principle be admitted to the ward as per local practice. In patients deteriorating despite 40–60 ml/kg fluid boluses, inotropes should be commenced, and the dose rate should be increased until stabilisation occurs. Admission to PICU with appropriate monitoring should be sought as per local practice.

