Primary clinical outcome	Survival free of organ dysfunction	• Organ dysfunction defined as pediatric Sequential Organ Failure Assessment (pSOFA) score >0. Patients dying within 28 days of presentation will be allocated zero days to correct for the competing effect of mortality on duration of organ dysfunction. Patients discharged alive from PICU to the ward or home not requiring ongoing support, and not being palliative, will be assumed to have no organ dysfunction after PICU discharge.
Secondary	Patient centered outcomes	• Survival free of inotrope support at 7 days • Survival free of multiorgan dysfunction at 7 days
		• 28-day mortality • Survival free of PICU censored at 28 days • PICU length of stay • Hospital length of stay • Functional Status Score and modified Pediatric Overall Performance Category at 28 days • Neurodevelopment, Quality of life and Functional status 6 months post enrolment
	Proxy measures of intervention efficacy	• Amount of fluid (mLs per kg) received during the first h, and by 4, 12, and 24 h post enrolment • Proportion with lactate <2 mmol/l at 6, 12, and 24 h post enrolment • Time to reversal of tachycardia during the first 24 h^*^. • Time to shock reversal, defined as cessation of inotropes for at least 4 h censored at 28 days

* *Goldstein et al. (22)*.

We consider a separation of ≥10 ml/kg fluid bolus administration during the first 24 h, and a difference in inotrope commencement time of ≥20 min between the two arms as an indication of feasibility of the protocol leading to a measurable and potentially clinically relevant difference in the treatment delivered.

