### Data Collection

Site visits for start up and ongoing education support are provided alongside a RESPOND ED specific resource booklet to assist in time-sensitive enrolment for clinicians and trial management. Demographic variables, severity at baseline, primary end points, secondary end points, proxy measures of intervention efficiency, feasibility measures, primary diagnoses, physiological parameters, diagnoses, therapeutic interventions and documentation of deaths and other serious adverse events will be prospectively recorded into a purpose-built REDCap online database (26), hosted by The University of Queensland (Table 3). All data will be collected by trained staff at each study site using a series of electronic case report forms (eCRFs) developed by the coordinating centre. Randomized patients will be followed up by study nurses until death or 28 days post-randomisation whichever occurs first, with a follow-up review performed 6 months after randomisation. Day-28 and 6-month follow-ups will occur by phone unless the patient is still in hospital. Details on long-term follow up will be published separately. Data collection will consider the following as inotropes or vasopressors: adrenaline, noradrenaline, vasopressin, milrinone, dopamine, dobutamine. The study protocol mandates the use of adrenaline as first line inotrope.

**Table 3 T3:** Study schedules to be captured in the study database.

**Study phase**	**Item**
Enrolment	• Screening & eligibility checks • Consent information • Baseline data including patient characteristics, treatment received, severity and physiology • Randomization
Interventions	• Time of and volume of fluid administered during first 24 h • Time of, type, and dose of inotropes administered
Early assessment	• Daily assessment of organ dysfunction using pediatric Sequential Organ Failure Assessment (pSOFA) • Organ support (respiratory and/or cardiovascular including extracorporeal membrane oxygenation, and renal support) • Laboratory markers of organ function and infection/inflammation
Late assessment	• Survival assessment at 28 days • Questionnaires by proxy on Functional Status Score and Pediatric Overall Performance Category at 28 days • Questionnaires by proxy on neurodevelopment, quality of life and functional status 6 months post enrolment

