### Statistical Analysis Plan

#### Sample Size

A recruitment period of 24 months is the projected time to achieve the required sample size of 40 participants. The size of the pilot (*N* = 40) was chosen to reflect about 10% of a full trial to yield sufficient data in relation to feasibility. We estimate that ~50 children each year are treated for septic shock in the main participating ED. Assuming that 30–40% of children will meet exclusion criteria, and anticipating 50% enrolment rates, completion within 24 months is projected to be feasible.

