#### Analysis

Using the Consolidated Standards of Reporting Trials (CONSORT) flow chart (Figure 1) (20), we will describe the number of screened patients, those meeting inclusion and exclusion criteria, the number consented, and numbers of those who withdrew consent. In addition, we will provide in the text details of the consent process, including proportion of children with prospective consent vs. consent to continue, reasons why consent to continue was used, and time from enrolment to obtaining written consent in hours (IQR). Time from randomisation to initiation of allocated treatment will be reported. Descriptive statistics will be utilised to report on demographics, clinical history and baseline clinical characteristics of patient allocated to each of the study arms (Supplementary Table 1). Statistical comparison between the characteristics of the two arms at baseline will not be undertaken. The feasibility and clinical outcome measures (Supplementary Tables 2, 3) will be compared with the estimate of the difference and corresponding 95% confidence intervals (CIs). Continuous outcomes are assumed to be non-normally distributed, and as such quantile regression will be used to generate the CIs. A test of two proportions will be used for the binary outcomes. Analyses will be by intention-to-treat. Adverse events will be presented descriptively (Supplementary Table 4).

We will graphically compare physiological measures, heart rate, systolic blood pressure, pulse pressure (systolic minus diastolic blood pressure), shock index (heart rate divided by systolic blood pressure) and use of fluid bolus volume (in ml/kg) over time, using values measured during the first 24 h, comparing the intervention group to the control group, using values measured during the first 24 h.

We anticipate that <30% of RESPOND ED study patients will be co-enrolled into a concomitant study investigating metabolic resuscitation, named RESPOND PICU (ACTRN12619000829112) (27). Given that the study is a pilot feasibility study, analyses on RESPOND ED will occur separately from RESPOND PICU.

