## Discussion

Resuscitation with intravenous fluid boluses represents a key element of paediatric sepsis treatment bundles (11, 13, 28). Despite the pathophysiological rationale for liberal fluid resuscitation, there is limited evidence for this practice, and potential for harm. Subsequent to the FEAST study conducted in a low resource environment where intensive care support was not available, no similar study powered for clinical endpoints was performed in high income settings (14, 29). As a result, current pediatric Surviving Sepsis Campaign guidelines maintained the recommendation to administer a 40–60 ml/kg fluid bolus in settings where intensive care is available, based on expert opinion rather than robust evidence (11).

Different to other pilot studies on the use of fluid in critically ill children with sepsis, which primarily regulated the amount of fluid to be administered (30, 31), the study protocol stipulates the early use of adrenaline rather than prescribing how much fluid should be administered thereafter. The present pilot study was designed to capture feasibility, process of care measures, and robust severity measures. In addition, the study encompasses a comprehensive follow-up of study patients at 28-days and at 6-months to assess patient-centred outcomes such as quality of life. The pragmatic study design, embedded in an established pediatric sepsis pathway, intends to facilitate enrolment to address challenges which have been observed in other fluid trials in children with sepsis (30, 31). However, the study sample size will not permit to conduct pre-planned adjusted analyses on clinical outcomes and the study is not designed to assess the impact of co-interventions such as steroids.

In summary, this pragmatic pilot study design will provide urgently needed data to inform feasibility and design of a full trial powered to assess benefit of early inotropes in sepsis.

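### The ≥10 mL/kg bolus separation has no time origin and is not adjusted for pre-randomisation volume, so it depends on an unstated counting rule and may lose some precision

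*Protocol article*

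**What the plan says.** The criterion is in the Protocol article, Study Outcomes, after Table 2: "We consider a separation of ≥10 ml/kg fluid bolus administration during the first 24 h". It is paired with a difference of at least 20 min in the start of inotropes, and the two are described as indicating feasibility. Neither this sentence nor the matching feasibility row of Table 2 gives a time origin. The separate proxy-efficacy row on fluid in Table 2 does: it counts from enrolment.

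On volume at entry, Inclusion and Exclusion Criteria says: "Randomisation will occur after participants have received at least 20mL/kg fluid bolus in the last 4 h", with 1,000 mL as the alternative above 50 kg. Table 1 lists as an exclusion: "Received ≥40 mL/kg of fluid boluses during the 4 h pre-enrolment". Randomisation is stratified by site only. Table 3 lists among the enrolment items: "Baseline data including patient characteristics, treatment received, severity and physiology".

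Standard Care sets the control arm on a total: "patients in the standard arm will receive 40–60 mL/kg of fluid bolus therapy prior to initiating inotropes". It then converts this to 20–40 mL/kg after randomisation.

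The Analysis section reports outcomes as a difference with a 95% CI, and for continuous outcomes "quantile regression will be used to generate the CIs". No covariate is named. The Discussion says that "the study sample size will not permit to conduct pre-planned adjusted analyses on clinical outcomes"; it says nothing of the kind about feasibility outcomes.

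**The concern.** Children enter with different volumes already given, and randomisation does not balance those volumes by design. If controls are managed to a total, a child who enters with 35 mL/kg has less still to receive than one who enters with 20. Entry volume is then related to the outcome by the protocol's own rule, and it is available at baseline, yet the planned comparison does not use it.

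The criterion also leaves open whether the qualifying bolus is part of the volume compared. With about 20 children per arm and a fixed mark of 10 mL/kg, a shift of a few mL/kg can decide on which side of the mark the estimate falls. An analyst who must choose the counting rule after seeing the data has a choice that the plan should have made.

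**Working it through.** **Inputs from the Protocol article.** Mark: 10 mL/kg (Study Outcomes). Size: "The size of the pilot (*N* = 40) was chosen to reflect about 10% of a full trial", allocated 1:1, so 20 per arm (Sample Size, Randomisation). Entry volume: at least 20 and under 40 mL/kg; above 50 kg the 1,000 mL rule allows less, for example 1,000/70 = 14.3 mL/kg. Neither the mark nor N is derived from a power, an alpha or an SD, so there is no sample-size figure to reproduce. The spread of entry volume is not given and is **assumed** below.

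**Step 1: the plan's own figure.** Standard Care: 40 − 20 = 20 and 60 − 20 = 40, so 20–40 mL/kg after randomisation reproduces, but only for entry at exactly 20. For entry at 30 the same total leaves 10–30. Under the total rule, entry volume therefore predicts later volume in controls; under a fixed 20–40 it does not.

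**Step 2: effect of the counting rule, means.** Let P be volume before randomisation, Y volume from randomisation to 24 h, and T = P + Y. Then

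difference in mean T = difference in mean Y + difference in mean P.

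The shift is the chance imbalance in P. Its SE is SD × √(1/20 + 1/20) = SD × 0.316. For P uniform on 20–40: SD = 20/√12 = 5.77, SE = 1.83, 95% limit = 1.96 × 1.83 = ±3.58 mL/kg (36% of the mark), average absolute size 1.46 mL/kg (15%).

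| Assumed entry volume (mL/kg) | SD | 95% limit | Average size |
|---|---|---|---|
| Uniform 20–30 | 2.9 | ±1.8 | 0.7 |
| 80% at 20, 20% at 30 | 4.0 | ±2.5 | 1.0 |
| Half at 20, half at 30 | 5.0 | ±3.1 | 1.3 |
| Uniform 20–40 | 5.8 | ±3.6 | 1.5 |
| 70/20/10% at 20/30/39 | 6.4 | ±4.0 | 1.6 |
| Half at 20, half just under 40 | 10.0 | ±6.2 | 2.5 |

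**Step 3: medians.** Quantile regression points to medians, although the quantile is not named. The identity in step 2 does not hold for them. In one simulation the unadjusted median separation moved by 2.8 mL/kg on average between the two countings. In another (uniform 20–40, controls managed to a 40–60 total, skewed later fluid) the shift averaged about −1.5 mL/kg rather than zero and correlated only about 0.6 with the imbalance in mean entry volume.

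**Step 4: what adjustment does.** If T = a + b·arm + c·P + error, then Y = T − P = a + b·arm + (c − 1)·P + error. Only the slope on P changes; the arm coefficient b is the same. This holds for least squares and for quantile regression, provided both windows end at the same time. In 600 simulated median regressions the two countings agreed in 96%; the average difference over all runs was 0.02 mL/kg, and the rest is put down to non-unique median solutions.

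**Step 5: precision.** Simulations with 20 per arm gave an SE change with adjustment from a reduction of about 40% to an increase of about 8% if the qualifying bolus counts, and about −6% to +5% if counting starts at randomisation.

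**Step 6: side of the mark.** With an assumed true separation of about 11–12 mL/kg, the two countings fell on different sides of 10 in about 9–21% of simulated trials by means and 16–26% by medians, leaving out the extreme last row. Another set of assumptions, with a true mean separation of 11.5, gave 10–13% and 9–13%.

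**The case against.** The strongest reply is that the counting question is largely answered elsewhere. The proxy fluid row counts from enrolment. Data Collection records study treatment from randomisation with totals at 1, 4, 12 and 24 h. Data Quality and Monitoring verifies boluses over the first 24 h of enrolment. Table 3 lists earlier treatment separately as baseline data. The likelier reading therefore leaves the qualifying bolus out, and on that reading adjustment gains little (about −6% to +5% in SE). This stands as to likelihood, but the criterion itself is silent, and the arms are defined on a scale that includes that bolus.

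Second, entry volumes may cluster near 20 mL/kg. Screening and Consenting advises a first bolus of that size, and the post-randomisation range in Standard Care presumes it. The 95% limit for means would then be nearer ±1.8 to ±2.5. This also stands; the documents do not settle the spread.

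Third, the true separation may be far from 10. One simulation with controls managed to the 40–60 total gave about 19–28 mL/kg, where a shift of this size would seldom matter. The disagreement rates in step 6 apply only near the mark.

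Fourth, covariates are often left to a separate analysis plan. That has less force here: the article presents itself as describing the analysis plan, states the method for this outcome, and gives a reason against adjustment that covers clinical outcomes only.

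A reader might go further and infer that the unadjusted comparison is biased. It is not: allocation is random, and the confidence interval already carries the chance imbalance.

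**Conclusion.** The point holds as a minor improvement to definition and precision. The criterion has no time origin, and a related baseline volume that is already recorded is left out of the comparison. For means, the counting rule is worth about 1.5 mL/kg on average with a 95% limit of ±3.6 if entry volume is uniform on 20–40, and limits of about ±1.8 to ±6.2 across other assumed spreads. For medians it can be larger and is not exactly the imbalance.

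Three stronger readings are not supported. A shift of a third of the mark is not typical: it is a 95% limit under an assumed spread. Chance imbalance and the counting rule are not two separate errors that add up: for means they are one effect. Nor does the trial stand or fall on this figure: Study Outcomes treats it as an indication of feasibility, beside the timing criterion and other feasibility measures.

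**What to change.** In Study Outcomes, state that the 24 h run from randomisation, and whether the qualifying bolus counts towards the volume compared.

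In Analysis, add a sentence such as: *The between-arm difference in 24 h bolus volume will be estimated with pre-randomisation bolus volume (mL/kg) as a covariate and reported with its 95% CI, alongside the unadjusted estimate.* Say in advance which of the two is set against the 10 mL/kg criterion; the adjusted one does not depend on whether the bolus counts, given the same end of the window.

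The authors should also reconcile the total and the post-randomisation range in Standard Care for children who enter with other than 20 mL/kg, since the relation between entry and later volume turns on it.

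The cost is two sentences and no new data item, because prior volume is needed to check eligibility and baseline treatment is already recorded. Adjustment uses one degree of freedom and can widen the SE by up to about 5–8% in some median-regression settings. In quantile regression it also gives a median difference conditional on entry volume rather than a marginal one, which is a reason to keep the unadjusted estimate beside it.

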### Study Interventions

Allocated treatment will be started as soon as possible after randomisation. The allocated intervention arm will be administered if the clinician is continuing to treat for signs of septic shock. The trial compares ***early inotropes*** started after 20 mL/kg fluid resuscitation with ***standard care*** (Figure 2).

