### Study Outcomes

This pilot study includes feasibility outcomes, as well as clinical primary and secondary outcome measures, and proxy measures of intervention efficacy (Table 2). The *feasibility outcomes* include consent rates; compliance measures such as time to inotropes, amount of fluid delivered during the first 24 h; and protocol violations. The *clinical primary outcome* is survival free of organ dysfunction, censored at 28 days. Organ dysfunction will be assessed by pediatric Sequential Organ Failure Assessment (pSOFA) scores (23). Patients dying within 28 days of presentation will be considered as zero days to correct for the competing effect of mortality on duration of organ dysfunction. Patients discharged alive from PICU to the ward or home not requiring ongoing respiratory or renal support, and not under palliative care will be assumed to have no organ dysfunction after PICU discharge. *Secondary clinical outcomes* include PICU free survival, survival free of inotrope support and free of multi-organ dysfunction (defined as >1 organ with a pSOFA score >0), mortality, and PICU and hospital length of stay. In addition, we will obtain Pediatric Overall Performance Category and Functional Status Score at 28 days (24). Long-term follow-up will be performed at 6 months post randomisation using assessment of quality of life using neurodevelopment, quality of life and functional status, and will be reported separately. *Proxy measures of intervention efficacy* include the proportion of study participants with a blood lactate level <2 mmol/L at 6, 12 and 24 h, time to reversal of tachycardia [defined by the upper age-specific thresholds for Systemic Inflammatory Response Syndrome (22)], and time to reversal of shock (defined as cessation of inotropes for at least 4 h). Ancillary studies assessing sepsis-related costs are pre-planned but will be reported separately.

**Table 2 T2:** Outcomes assessed.

**Outcome**	**Criterium**	**Definition**
Feasibility of the protocol	Compliance with study protocol	• Recruitment rates; proportion of eligible randomised, proportion of eligible consented using prospective consent and consent to continue. • Time to initiation of inotropes between the control and the early inotrope arm • Amount of fluid delivered (in mLs per kg) during the first 24 h between the control and the early inotrope arm • Protocol violations

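### The 20-minute inotrope-separation criterion has no rule for children who never start inotropes, and counting them or leaving them out can change whether it is met

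*Protocol article*

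**What the plan says.** Table 2 lists among the feasibility outcomes "Time to initiation of inotropes between the control and the early inotrope arm". The text below the table takes "a difference in inotrope commencement time of ≥20 min between the two arms as an indication of feasibility of the protocol", alongside a separation of at least 10 mL/kg in bolus fluid over 24 h. It names no summary measure, time origin or horizon for the inotrope time.

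Under Standard Care, "In patients deteriorating despite 40–60 ml/kg fluid boluses, inotropes should be commenced". Other inotrope decisions in that arm are left to the treating doctor, and "Patients who improve in <4 h can in principle be admitted to the ward as per local practice". Under Early Inotropes, adrenaline is to start straight after randomisation, but Study Interventions adds a condition that covers both arms: "The allocated intervention arm will be administered if the clinician is continuing to treat for signs of septic shock".

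On method, the Analysis section says "Continuous outcomes are assumed to be non-normally distributed, and as such quantile regression will be used to generate the CIs" and "Analyses will be by intention-to-treat". Another time outcome in Table 2 does have a limit: "Time to shock reversal, defined as cessation of inotropes for at least 4 h censored at 28 days".

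**The concern.** The outcome is an event time that some children will not have, and the assigned method is the one for ordinary continuous measurements. A standard-arm child who improves on fluid and goes to the ward contributes no commencement time. Such gaps should fall mostly in one arm and be linked to prognosis.

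An analyst who puts the recorded times into a quantile regression compares the controls who needed inotropes with the early-arm children who received them. That is not the randomised comparison. If the absent controls are those who would have started latest, the remaining controls look early and the gap shrinks, although treatment in the two arms differed more. An analyst who keeps non-starters as the latest times gets a different answer from the same data. With about 20 children per arm and an open-label design, that choice should not be left until the times are known.

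**Working it through.** **Inputs from the article.** N = 40 with 1:1 allocation, so about 20 per arm; threshold 20 min; quantile regression; intention-to-treat. The threshold is set by judgement, so there is no plan figure to reproduce.

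**Inputs assumed, because the article gives none.** The proportion p of controls who never start is varied from 20% to 60%. Start times are lognormal: early-arm median 20 min (log-SD 0.6); control median 60 min, or 45 min as a variant (log-SD 0.8), if every control eventually started.

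**Step 1: when is the control median not reached?** With 20 controls, the midpoint of the 10th and 11th ordered times has no finite value if 10 or more never start. The chance is the sum over k = 10 to 20 of C(20,k) p^k (1−p)^(20−k):

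| p | Chance |
|---|---|
| 20% | 0.3% |
| 30% | 4.8% |
| 40% | 24% |
| 50% | 59% |
| 60% | 87% |

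**Step 2: what does dropping non-starters do if the slowest controls are the ones who never start?** The starters' median is then the (1−p)/2 quantile of the underlying control times, 60 × exp(0.8 × z), where z is the normal quantile at (1−p)/2.

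- p = 20%: z = −0.253, median 49.0 min, gap 49.0 − 20 = 29.0 min.
- p = 40%: z = −0.524, median 39.4 min, gap 39.4 − 20 = 19.4 min.
- p = 60%: z = −0.842, median 30.6 min, gap 30.6 − 20 = 10.6 min.

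If non-starters are kept as the latest times, the control median stays at 60 min while p is below one half, and the gap is 60 − 20 = 40 min. Simulation of 4,000 trials with 20 per arm agrees (kept = non-starters set to 24 h):

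| p | Gap, kept | Gap, dropped | Chance of ≥20 min, kept | Chance of ≥20 min, dropped |
|---|---|---|---|---|
| 20% | 39.9 | 28.8 | 96% | 81% |
| 40% | 40.2 | 19.4 | 96% | 47% |
| 60% | about 1,419 (set by the cap) | 10.4 | 96% | 6% |

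With a control median of 45 min and p = 40%, the gap is 25.3 min kept and 9.5 min dropped. The chance of meeting the criterion is 69% against 6%.

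**Step 3: does it depend on who the non-starters are?** Yes. If never starting is unrelated to how late a child would have started (60-min case), dropping gives 40.4 min at p = 20% and 40.6 min at p = 40%, essentially unchanged. Keeping them gives 57.9 and 115.0 min. The two analyses still differ, but both pass.

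**Step 4: one simulated trial by median regression.** With the slowest 8 of 20 controls never starting:

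- Dropped: 27.5 min (95% CI 7.4 to 47.7, n = 32).
- Kept: 56.3 min (34.4 to 78.3, n = 40), whether the late value is 24 h or 28 days.

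With 12 of 20 never starting, dropping gives 7.7 min. Keeping gives 1,421 min with a 24 h cap and 40,301 min with a 28-day cap, so the result is nothing but the cap.

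**The case against.** A reader might infer that the plan excludes non-starters, or that the comparison cannot be computed. The article supports neither. It nowhere says non-starters are dropped, and intention-to-treat points the other way. Median regression can rank them as latest, and the result is then computable and does not depend on the cap while fewer than half of an arm never start.

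A reader might also infer that the measured gap must move in the wrong direction. That holds only if never starting goes with a later start (Step 3). Nor need the criterion fail. With an early-arm median of 25 min, a control median of 90 min and mostly the mildest children not starting, the starters-only gap falls from 65 min to 46, 36 and 32 min at 30%, 50% and 60% non-starters, and every value still passes.

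Three further points stand. Only children still being treated for shock after the first 20 mL/kg are randomised, which may keep the non-starter rate down. Early-arm children may also never start. The criterion is called an indication, next to a fluid criterion that does not depend on starting inotropes, and no formal decision rule is attached.

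It can also be said that an article condenses, and that its supplementary tables are not shown. That carries less weight here. The article says that it describes the statistical analysis plan, and it states the threshold, the method and the population. Those three do not fit an outcome that the standard-arm rules leave without a value for some children.

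**Conclusion.** The point holds as a mismatch between outcome and method. The 20 min criterion has no defined value for children who never start inotropes, the article's own treatment rules make such children likely, and the stated analysis has no censoring rule for them. A starters-only analysis would depart from intention-to-treat and can move the result across the threshold: about 40 min against 19 min at 40% non-starters, with the chance of meeting the criterion at 96% against 47%. If half or more of an arm never start, its median is not reached.

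These sizes rest on assumed start times and non-starter rates, and the direction rests on the slowest or mildest controls being the non-starters. Severity is moderate: one of two separation indications is affected, and there is no formal go/no-go rule.

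**What to change.** Before analysis, define the outcome as time from randomisation to first inotrope in all randomised children, in both arms. Censor non-starters at a stated horizon and do not exclude them; 24 h, for example, matches the period over which study treatment is recorded. Apply the 20 min criterion to the difference in Kaplan-Meier or censored-quantile medians with a 95% CI. If the control median is not reached, report it as such, without substituting a number. Beside it, report the proportion starting inotropes per arm, for example by 1, 4 and 24 h. Keep the starters-only median as a descriptive figure.

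A restricted mean difference may be added as support but should not carry the 20 min threshold, because it mixes delay with never starting. If starters in both arms began at 60 min and non-starters counted as 240 min, a 12-point excess of control non-starters alone would give 0.12 × (240 − 60) = 21.6 min and meet the criterion with no difference in delay.

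The cost is wording only. Table 3 already includes the time of inotrope administration.
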